### Database and data management

The study database was designed in Microsoft Access based desktop application. The database developed is 21 CFR Part 11 compliant, i.e. it has an inbuilt audit trail function to capture each and every data entry activity, records details of users who access the database with date and time and electronic signature. The scanned forms are received via secured FTP server at the study central coordinating centre in New Delhi, where the data are collated, cleaned, and analysed.

### Study intervention

The test supplements were capsules with either algal DHA or placebo (soy/corn oil in 50:50 ratio). Each DHA capsule contains 200 mg of DHA derived from an algal source. The placebo capsules contained an equal amount of corn/soy oil. All participating women received either 2 placebo or DHA capsules from ≤20 weeks of gestation until 6 months postpartum. The total dosage of DHA being given via active capsules was 400 mg/d (2 X 200 mg). The active and placebo capsules used were identical with respect to taste and appearance and only differed in coding.

#### Manufacture

Identical capsules for the intervention and control groups were provided by DSM Nutritional Products, Mumbai. They were received by the bottling vendor who packaged the batch into white opaque bottles with 15 days supply (30 plus 5 extra for spillage = 35) in each. These bottles were coded the bottling warehouse by staff not involved directly in the study. The supplements were then couriered to the site and provided to women by trained fieldworkers during fortnightly visits at the participant’s home or workplace. The shelf life of each batch of capsules is close to 2 years at room temperature (25 °C).

#### Administration

A fortnightly schedule was drawn up for each woman from the day of her randomization. Supplements were provided by field workers during home visits. If informed about travel plans by the participant, study staff provided more than 1 bottle at a time. The women were instructed to take two capsules daily, preferably, at the same time each day. All the women also received iron-folic acid tablets for 100 days as per the Government of India policy.

### Monitoring adherence

Compliance for each woman was recorded in a basic form (15 days record) in which the participant marked with a tick if she consumed the capsule. In case she expressed any difficulties completing the form, the FW followed up by asking her details during home visits. The 2 weeks’ record along with the left over/unused capsules in the bottle of the supplements was collected by field workers from the participants’ home. During the home visit, the field worker also recorded details of any side effects, adverse event or illness and capsule count in a follow-up record form (Compliance Form). Weekly reminder phone calls were done for each mother by study personnel. Compliance is calculated as the total number of capsules actually consumed, expressed as a percentage of the total number expected to be consumed.

### Blinding

All study participants and members of the study team were blinded to the treatment scheme throughout the intervention period of the study. Data will be unblinded for the analytical study team after the last baby born in the study turns 1 year of age. Since the study may be extended for follow-up of child development, participants and field personnel will remain blinded to the treatment allocation.

### Emergency unblinding

Unblinding will only be performed if the number of serious adverse events (SAEs) observed during the trial is significantly higher in one group than the other. The final discretion to make this call will that be of the DSMB.

### Reporting of adverse events

Adverse events (AEs) or SAEs (hospital admission, maternal or fetal or child death, abruption placenta, congenital anomaly, any other medically significant event) are reported as soon as (within 24 h of knowing) possible by the project officer to the study physician, who in turn examines and notifies the site principal investigator about the nature and severity of the AE. The study’s site principal Investigator (PI) notifies all serious AEs within 24 h to the trial Principal Investigator, Institutional Review Boards (IRBs). The DSMB is also notified each time. A summary quarterly report to DSMB and annual report to the ethics committees is also being submitted for their perusal. Table 3 lists the expected AEs and SAEs.

### Compensation

Clinical trial insurance has been procured to compensate clinical trial participants where required (Policy Number OG-17-1401-3306-00000001). Also, the participants are being compensated for their travel expenses when they are called for follow up assessments.

#### CONSORT statement

All pregnant women screened for eligibility in this trial will be accounted for and a CONSORT statement will be prepared (http://www.consort-statement.org). Reasons for early withdrawal will be listed for all participants who prematurely discontinued treatment or left the study. The number of participants who were screened eligible but not randomized are presented and the reasons for non-participation (where available) are recorded. A diagram mapping the flow of participants to date is provided (Fig. 1- CONSORT diagram). Recruitment started on 6th Jan 2016 and ended on 31st Aug 2017. We had expected to enroll 1000 women by March 2017 but were delayed by an unexpected capsule shortage, as a result of which we could not recruit for about 4 months. The final number recruited and randomized is 957. About 70% of the enrolled mothers have delivered so far and 15% have completed the trial.

**Fig. 1 Fig1:**
[figure not shown]
CONSORT Diagram

### Statistical analyses

All the analyses will be performed on the principle of ‘intention to treat’ unless otherwise specified (i.e., we will compare patients in the groups to which they were originally randomly assigned). Statistical analyses will be performed using STATA Version 14.0. We will summarize maternal and household characteristics in the two groups and assess the effectiveness of randomization by comparing these between the groups. Continuous, normally distributed variables will be summarized as means and standard deviations, while skewed variables will be summarized as medians and inter-quartile ranges. Categorical/binary variables will be summarized using proportions. Comparisons on baseline characteristics will also be made between the final study sample and those who were lost to follow up.

For the primary outcome, we will test the unadjusted difference in the mean DASII score at 6 months and 12 months between the two treatment groups using a two-sample t-test. For adjusted analyses, we will consider the DASII score as a continuous variable and use a multiple linear regression model, adjusting for treatment, sex of the child, maternal age, maternal education, socio economic status, birth-weight and other factors which we find out to be significant at baseline comparison. We will adjust for the 6 month DASII score in the model examining the difference in score at 12 months between the treatment groups using Generalized Estimating Equation (GEE) analyses to account for correlation between the 6 month and 12 month DASII score.

The DASII score will also be analysed as a binary variable. DASII score ≤ 70 will be used to defined developmental delay. The unadjusted and adjusted relative risk in the proportion of DASII score (≤70) at 12 months between DHA and placebo groups will be calculated using a log-binomial regression. In case of convergence issues with the log-binomial model, logistic regressions will be used to conduct the adjusted analyses and adjusted odds ratios will be reported instead of adjusted relative risks.

The differences in weight, length, head circumference, still birth, Apgar score at 1 min & 5 min of the infants at birth will be tested using t-test. Adjusted analyses will be performed using multiple linear regression.

For longitudinal analysis of weight, length and head circumference (i.e. at birth, 1 month, 6 month and 12 month), we will also compare the average growth trajectories of the infants between the treatment and placebo groups using Generalized Estimating Equation (GEE) models. The adjusted analyses will also be performed adjusting for time, maternal weight and height, breast-feeding practices and maternal dietary intake.

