**Methods:**

DHANI is a double-blinded, parallel group, randomized, placebo controlled trial supplementing 957 pregnant women aged 18–35 years from ≤20 weeks gestation through 6 months postpartum with 400 mg/d algal-derived DHA or placebo. Data on the participant’s socio-demographic profile, anthropometric measurements and dietary intake are being recorded at baseline. The mother-infant dyads are followed through age 12 months. The primary outcome variable is infant motor and mental development quotient at 12 months of age evaluated by Development Assessment Scale in Indian Infants (DASII). Secondary outcomes are gestational age, APGAR scores, and infant anthropometry. Biochemical indices (blood and breast-milk) from mother-child dyads are being collected to estimate changes in DHA levels in response to supplementation.

All analyses will follow the intent-to-treat principle. Two-sample t test will be used to test unadjusted difference in mean DASII score between placebo and DHA group. Adjusted analyses will be performed using multiple linear regression.

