
In summary, studies conducted to date suggest that improvements in DHA levels in mother may confer some benefit for child neurodevelopment. Furthermore, DHA appears to be safe, with no adverse birth outcomes related to DHA supplementation observed in low- risk pregnancy cases [34]. Very few studies to date have continued supplementation through lactation. We therefore implemented a large scale randomized trial to study the effects of pre- and post-natal DHA supplementation on birth weight, gestational age and neurodevelopment in India, a country with low DHA intakes and a high dietary n-6 to n-3 ratio. This will be the first to examine the effects of in-utero and early life DHA exposure (through maternal supplementation from mid-pregnancy through 6 months postpartum) on postnatal neurodevelopment and body-size of Indian infants. Long term contact and follow-up with this cohort is being planned. The biological specimens being collected (blood, cord-blood, and breast-milk) from the mother-child dyads can further help pursue new hypotheses and unravel critical information about early DHA intervention on later life of an individual [35–41].

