## Methods

### Study design

DocosaHexaenoic Acid supplementation during pregnancy and lactation on Neurodevelopment of the offspring in India (DHANI) is a double-blinded, randomized, placebo controlled trial being conducted in India. Study participants are healthy pregnant women and their offsprings.

DHANI will assess the impact of 400 mg of pre- and post-natal DHA supplementation (from ≤20 weeks of gestation to 6 months postpartum) on infant neurodevelopment at 6 and 12 months as measured by the Development Assessment Scale for Indian Infants (DASII). Secondary objectives of this trial include an assessment of the impact of maternal DHA supplementation on: gestational age, new born anthropometry (birth weight, length and head circumference) and APGAR score; infant anthropometry (birth weight, length and head circumference) at birth, 1 month, 6 months and 12 months; number of unfavorable pregnancy outcomes (still births, low birth weight babies, preterm babies); morbidity patterns through 12 months in the two groups. The first mother was enrolled on 6 Jan 2016 and the last on 31st Aug 2017. The data being collected under the trial for mother-infant dyads at each time point has been presented in Table 1.

**Table 1 Tab1:** Data being collected under DHANI trial

Domain	Measure	Data obtained on woman						Data obtained on child		
		Pregnancy		Delivery	Post partum/ lactation			Birth	6 months	12 months
		Enrolment at < =20 weeks	Each month until Delivery	Delivery	2-3rd Day Post partum	1 month Post partum	6 month post partum			
Socio-economic and demographic profile	Demographics	X								
	family details	X								
	Income	X								
	Education	X								
	Occupation	X								
Medical and Obstetric History	Clinical Investigation	X	X	X	X		X	X	X	X
	Obstetric History	X								
	Complications	X	X	X	X	X	X	X	X	X
	Adverse events	X	X	X	X	X	X	X	X	X
	Eligibility	X								
Blood	Fatty acid composition	X		X			X	X	X	X
Breast milk (30%)	Fatty acid composition				X	X	X			
Body Size & composition	Anthropometry (weight, length, mid upper arm circumference, head circumference of offspring)	X	X	X	X	X	X	X	X	X
Behavioral Factors	Dietary Intake	X							X	X
	Physical activity	X					X			
	Prenatal Care	X	X							
	Substance use	X								
Child development	APGAR							X		
	Developmental Quotient								X	X
	Morbidity	X	X	X	X	X	X	X	X	X

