#### Secondary outcome(s)

Difference in proportions of infants with developmental delay between the DHA and placebo group at 12 months. Developmental delay will be defined as a DASII score ≤ 70.Mean difference in infant size (weight, length and head circumference) and APGAR score at birth.Mean change in infant size (weight, length and head circumference) at birth, 1 month, 6 months and 12 months between the DHA and placebo group.Mean difference in number of still births, preterm and low birth weight babies between DHA and placebo groups.Difference in infant morbidity patterns (types of illness, frequency and duration of specific conditions) between DHA and placebo group.

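### The adjusted DASII model includes birth weight, a post-randomisation trial outcome, so its treatment coefficient need not be the total effect of assignment

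*Protocol article*

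**What the plan says.** The Statistical analyses section first compares mean DASII scores between groups with a two-sample t-test. It then plans a multiple linear regression for DASII, "adjusting for treatment, sex of the child, maternal age, maternal education, socio economic status, birth-weight" and any factors found significant when the groups are compared at baseline. The section defines intention to treat as comparing women in the groups to which they were randomised.

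The Methods part of the abstract says the women are supplemented "from ≤20 weeks gestation through 6 months postpartum with 400 mg/d algal-derived DHA or placebo". Birth weight is therefore recorded after randomisation and during treatment.

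The article treats birth weight as something DHA may affect in four places:

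- Trial purpose (DHA and neurodevelopment): "to study the effects of pre- and post-natal DHA supplementation on birth weight, gestational age and neurodevelopment in India".
- Secondary objective (Study design): "impact of maternal DHA supplementation on: gestational age, new born anthropometry (birth weight, length and head circumference".
- Secondary outcome (Secondary outcome(s)): "Mean difference in infant size (weight, length and head circumference) and APGAR score at birth".
- Between-group test (Statistical analyses): "The differences in weight, length, head circumference, still birth, Apgar score at 1 min & 5 min of the infants at birth will be tested".

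The adjusted DASII regression is nowhere described as a mediation or direct-effect analysis.

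**The concern.** The Statistical analyses section uses one variable both as an outcome of treatment and as a covariate. Covariate adjustment in a randomised trial is safe when the covariates cannot be affected by treatment. Birth weight can be. A woman who enters at 20 weeks or earlier and delivers at 37 weeks or later has at least 37 − 20 = 17 weeks of supplementation before her baby is weighed.

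With birth weight held fixed, the treatment coefficient answers a different question: how DASII differs between arms among infants of the same birth weight. Any benefit that comes through better fetal growth is taken out. The coefficient need not be a clean direct effect either. Causes shared by birth weight and development that are not in the model become unbalanced between arms once birth weight is conditioned on, if DHA affects birth weight. At stake is the interpretation of the adjusted result for the primary outcome, which readers would naturally take as a more precise version of the unadjusted one.

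**Working it through.** **1. The plan's own figure.** Inputs from Effect size, power and sample size: effect 0.25 SD, two-sided α = 0.05, power 90%, 338 infants per group.

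n per group = 2 × (1.960 + 1.282)² / 0.25², which rounds up to 337 by the normal approximation. The t-based solution is 337.2, which rounds up to 338. Power at 338 per group is 0.901. The stated figure reproduces, so this point does not rest on a sample-size error.

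**2. What the adjusted coefficient estimates.** Work in SD units with a linear model. Let

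- T = total effect of assignment on DASII (0.25 in the planning scenario),
- a = effect of DHA on birth weight,
- s = within-arm slope of DASII on birth weight.

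Then the adjusted coefficient = T − a × s.

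If birth weight affects DASII with slope b, and an unmeasured common cause acts on birth weight (g) and on DASII (h), then s = b + g × h. The direct effect is T − a × b, so the adjusted coefficient equals the direct effect only when g × h = 0 or a = 0. It equals T when a = 0.

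**3. Illustrative size.** The documents give neither a nor s; both are assumed here. Adjusted coefficient for T = 0.25 (share of the effect removed in brackets):

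| a | s = 0.2 | s = 0.3 | s = 0.4 |
|---|---|---|---|
| 0 | 0.25 (0%) | 0.25 (0%) | 0.25 (0%) |
| 0.1 | 0.23 (8%) | 0.22 (12%) | 0.21 (16%) |
| 0.2 | 0.21 (16%) | 0.19 (24%) | 0.17 (32%) |
| 0.3 | 0.19 (24%) | 0.16 (36%) | 0.13 (48%) |

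For example, 0.25 − 0.2 × 0.3 = 0.19, and 0.06 / 0.25 = 24%.

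**4. Power of the adjusted model in the same scenarios.** The standardised effect is (0.25 − a × s) / √(1 − s²), with 338 per group.

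- a = 0.1, s = 0.2: 0.23 / 0.980 = 0.235, power about 86%.
- a = 0.2, s = 0.3: 0.19 / 0.954 = 0.199, power about 73%.
- a = 0.3, s = 0.4: 0.13 / 0.917 = 0.142, power about 45%.
- a = 0: power rises slightly, to about 91% at s = 0.2 and 93% at s = 0.3, because birth weight then only reduces residual variance.

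These figures belong to the adjusted model alone. The t-test keeps its planned 90%.

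**5. Common-cause example.** Assume a = 0.2, b = 0.2, g = h = 0.5. Then s = 0.2 + 0.25 = 0.45 and the adjusted coefficient = 0.25 − 0.2 × 0.45 = 0.16. The direct effect would be 0.25 − 0.04 = 0.21. A simulation of 2,000,000 records gave 0.250 without birth weight in the model and 0.159 with it, in line with the algebra. The adjusted figure is neither the total nor the direct effect.

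**The case against.** The strongest answer is that the primary outcome already has a sound test. The t-test comes first, does not condition on birth weight, and is the comparison that 338 per group was sized for. The regression is an additional analysis and is never called the primary one. That stands. A reader might infer that the primary test is compromised or that its power falls below 90%; the documents do not support this.

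A reader might also infer that the model breaks the intention-to-treat commitment. It does not break the protocol's own definition, because the regression still compares women as randomised. What changes is the quantity estimated.

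It is also fair to say that the loss is not certain. The protocol sets out to study birth weight as a possible effect and asserts none. With a = 0 nothing is removed, and the upper scenarios need a birth-weight effect larger than the 0.25 SD on which the primary outcome is powered. At (0.1, 0.2) and (0.2, 0.3) the shifts of 0.02 and 0.06 SD are smaller than the standard error of the group contrast, √(2/338) = 0.077 SD. It would be wrong to say that the two analyses must disagree.

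Finally, the adjusted growth model, "adjusting for time, maternal weight and height, breast-feeding practices and maternal dietary intake", may look like the same error because breast-feeding follows randomisation. The documents do not show that it is. Feeding practice is not listed as an outcome, and nothing suggests that blinded capsules change it. DHA may change milk composition, but adjusting for practice does not hold composition fixed.

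None of this justifies birth weight as a covariate. A trial designed partly to learn whether DHA changes birth weight cannot assume in its adjusted primary-outcome model that it does not.

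**Conclusion.** The point holds for the adjusted DASII regression only. Birth weight is a post-randomisation, on-treatment outcome of this trial, and with it in the model the treatment coefficient does not in general estimate the total effect of assignment. The bias is zero under linearity if DHA leaves birth weight unchanged. Otherwise it is a × s, and its direction follows the sign of that product. Under the assumed ranges (a from 0 to 0.3 SD, s from 0.2 to 0.4), a true 0.25 SD effect would be reported as 0.25 down to 0.13 SD. These are scenarios, not estimates, because the documents give neither quantity. Since the unadjusted test is intact and the size may be nil, this is a should-fix matter.

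**What to change.** Delete birth weight from the adjusted DASII models. Adjust only for variables fixed before randomisation, plus infant sex, which treatment from mid-pregnancy cannot alter. If the fetal-growth pathway is of interest, report a model with birth weight separately, label it an exploratory mediation analysis, and state its assumption of no unmeasured common causes.

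The cost is one line of wording and no data. Some precision is given up: at an assumed slope of 0.2 to 0.4, birth weight would shrink the standard error by a factor of √(1 − 0.04) = 0.98 to √(1 − 0.16) = 0.92, that is, by 2% to 8%. The sample size did not rely on this gain.

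The article reports about 15% of mothers as having completed the trial, and the analysts are unblinded only after the last infant turns one, so as described the change can be made without knowledge of results. The 6-month DASII score in the 12-month model is a separate question and is not judged here.

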### Effect size, power and sample size

The primary outcome variables are infant motor and mental development quotient at 12 months of age. The smallest effect sizes of interest were 0.25 S.D. for motor and mental development at 12 months of age [42]. Using a two-tailed test and a significance level of α = 0.05, a final sample of 338 infants per group (676 mother-child dyads) was required at the end of the study (12 months postpartum) to provide 90% power. A total of 957 mothers have been recruited in the present study, allowing for potential attrition due to serious adverse events, withdrawal, and migration out of the study area. Breast-milk samples are being collected within 3–4 days after delivery and at 1 month and 6 months postpartum from a 30% convenience sub-sample - 150 mother-infant pairs per group, which will have 95% power to detect effect sizes of 0.5 S.D. in DHA levels.

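### Extra covariates for the adjusted DASII regression are chosen by significance of baseline differences, with no threshold, candidate list or lock before unblinding

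*Protocol article*

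**What the plan says.** Under Statistical analyses, the protocol article tests the unadjusted DASII difference "between the two treatment groups using a two-sample t-test". It then sets out a multiple linear regression "adjusting for treatment, sex of the child, maternal age, maternal education, socio economic status, birth-weight" and, in addition, "other factors which we find out to be significant at baseline comparison".

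The baseline comparison is introduced in the preceding paragraph, where the authors will summarise maternal and household characteristics and "assess the effectiveness of randomization by comparing these between the groups". That paragraph also plans a second baseline comparison, of the final sample with those lost to follow-up. The covariate clause does not say which comparison it means; between treatment groups is the natural reading. No significance level and no set of candidate factors is given.

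On timing, the Blinding section says: "Data will be unblinded for the analytical study team after the last baby born in the study turns 1 year of age". No section dates the choice of covariates.

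**The concern.** A covariate earns its place in an adjusted model by predicting the outcome. Under the blocked randomisation described in the article, a baseline difference between the randomised groups is a chance event. A small p-value for it neither shows that randomisation failed nor says whether the factor predicts DASII. A rule built on that p-value therefore selects on the wrong property: a strong predictor that is balanced stays out, and an irrelevant factor that is imbalanced goes in.

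Without a threshold or a candidate list, two analysts who follow the text in good faith could fit different models. Nothing in the article rules out making the choice once treatment labels and 12-month outcomes are both available. At stake is the credibility of the adjusted estimate for the primary outcome, and some precision.

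This is more than detail left to an analysis plan. The article states a selection rule, and the rule is a poor one.

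**Working it through.** **Inputs from the article** (Effect size, power and sample size): "The smallest effect sizes of interest were 0.25 S.D. for motor and mental development at 12 months of age"; "Using a two-tailed test and a significance level of α = 0.05"; 338 infants per group, 676 in total, "to provide 90% power".

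**Assumed inputs**, because the article gives neither: the number of candidate factors k, and the share R² of DASII variance that the covariates explain.

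**1. The plan's own figure.** Normal approximation: n = 2(1.960 + 1.282)²/0.25² = 336.2, so 337 per group. The t-test gives 337.2, so 338, as stated. Power at 338: SE = √(2/338) = 0.0769 SD; 0.25/0.0769 = 3.25; Φ(3.25 − 1.96) = 90.1%. The stated size is that of the unadjusted t-test, which the covariate clause does not touch.

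**2. How often chance alone adds a covariate.** With k independent candidates tested at 0.05, P(at least one significant) = 1 − 0.95^k.

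| k (assumed) | Expected number significant | P(at least one) |
|---|---|---|
| 5 | 0.25 | 23% |
| 10 | 0.50 | 40% |
| 20 | 1.00 | 64% |
| 30 | 1.50 | 79% |

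Table 1 of the article marks 17 measures at enrolment. Some cover several variables, and others, such as eligibility, are not candidates. A range of 10 to 20 is plausible, but it remains an assumption.

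**3. Precision forgone.** With a fixed covariate set, power = Φ(0.25/[√(1 − R²) × 0.0769] − 1.96).

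- R² = 0.20: Φ(3.634 − 1.96) = 95.3%
- R² = 0.25: Φ(3.753 − 1.96) = 96.4%
- R² = 0.30: Φ(3.885 − 1.96) = 97.3%

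If the five named covariates already explain 0.20 and further prognostic factors would raise this to 0.25–0.30, leaving those factors out costs 96.4 − 95.3 = 1.1 to 97.3 − 95.3 = 2.0 points of power.

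**4. Behaviour of the rule if it were the only source of covariates.** Simulation: 338 per group, 6,000 trials per setting, three prognostic factors among k candidates, selection at p < 0.05. All entries are percentages.

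| R², k | Type I: unadjusted / rule / fixed set | Type I: significant on unadjusted or rule | Power: unadjusted / rule / fixed set |
|---|---|---|---|
| 0.10, 10 | 4.7 / 4.6 / 4.8 | 5.1 | 89.9 / 90.0 / 92.6 |
| 0.20, 10 | 5.6 / 5.1 / 5.7 | 6.0 | 89.8 / 90.3 / 94.8 |
| 0.30, 10 | 5.1 / 4.3 / 4.9 | 5.4 | 90.7 / 91.8 / 97.1 |
| 0.30, 20 | 4.8 / 3.9 / 5.0 | 5.2 | 90.2 / 91.0 / 97.0 |

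The Monte Carlo standard error for a 5% rate is √(0.05 × 0.95/6,000) = 0.28 points. In every setting the rule rejects under the null slightly less often than the unadjusted test, and its power is no lower. Counting a trial as positive if either analysis is significant adds 0.3 to 0.4 points to the unadjusted error rate. These settings omit the five fixed covariates, so their gap in power between the rule and a fixed set overstates the loss under this plan. Step 3 is the relevant figure.

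**The case against.** The best defence is that the clause governs only an accompanying regression. The unadjusted t-test stands, the sample size rests on it, and five covariates are fixed in any case. One irrelevant covariate among 676 infants costs almost nothing. Candidates such as income, education and occupation are probably correlated, which would lower the 40% to 64%. All of this stands, and it limits the size of the point.

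A further argument is that imbalance among the infants analysed need not be pure chance: 957 women were recruited and 676 infants are needed, so up to 1 − 676/957 = 29.4% may be lost. That is fair, but differential loss is a missing-data problem, and the article plans sensitivity analyses for it. It does not turn a significance test into a measure of prognostic value.

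Three stronger readings are tempting, and the article does not support them.

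- *The analysts will choose covariates after unblinding.* A reader might infer this from the Blinding section, since a between-group comparison needs group labels. But the article does not date the choice. Enrolment had closed, so the comparison could be run on coded arms before outcomes are complete. What can be said is that nothing requires this.
- *The rule wastes planned power, or loses most of the available precision.* It does not take power below the planned 90%, and the five named covariates are adjusted for regardless.
- *The rule inflates type I error.* Applied mechanically, it is slightly conservative if anything. The effect of discretionary choice is not quantified here.

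**Conclusion.** The point holds in a limited form. The rule for extra covariates selects on chance imbalance and not on prognosis. It has no threshold or candidate list and need not be settled before unblinding. The content of the adjusted DASII model is therefore partly a matter of luck and open to choice: at least one chance addition in 40% to 64% of trials, assuming 10 to 20 independent candidates tested at 0.05.

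The main fault is lack of pre-specification. The numerical cost is modest, about 1 to 2 points of power, assuming R² of 0.20 from the named covariates and 0.25–0.30 with further prognostic ones. The conclusion about the rule itself depends on none of these assumed figures. The unadjusted primary test is not in question. The change is worth making because it is nearly free and the adjusted estimate concerns the primary outcome.

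**What to change.** Delete the clause, and do not use significance tests of baseline differences to select covariates; a descriptive baseline table is enough. Name one definite list of pre-randomisation prognostic covariates that are already collected. For example, keep infant sex (fixed at conception although recorded at birth), maternal age, maternal education and socio-economic status, and add gestational age at enrolment, maternal BMI and parity. State how each enters the model, lock the list before the analysts are unblinded, and use it whatever the baseline table shows.

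Birth weight is measured after randomisation and is itself a trial outcome. Whether it stays in the model is a separate question, to be decided explicitly.

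The cost is a few lines of analysis-plan wording, with no new data. The article reports that 15% of enrolled mothers had completed the trial, so at that point the list could still be locked before unblinding.
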